### Randomization, allocation, and masking of study groups

Women who want to participate in the trial who fulfill the study criteria will be assigned consecutive numbers and will be allocated to one of the two study groups using a simple – not stratified – random number sequence using a computer program generated by a member of the research team who does not know the study aims. The allocation will be carried out by a researcher of the “Primary Care Prevention and Health Promotion Research Network” (REDIAPP) who is not involved in the study. The number sequence will be concealed until intervention groups are assigned. Thus, participants will have to agree to participate in the study before the randomization process and will not be informed of their group allocation until after completion of the pre-treatment measures. Because of the nature of the intervention, participants cannot be blinded to their group allocation. Study personnel conducting psychological assessments will be masked to participants’ treatment conditions and will be specially advised not to ask for this information. The researcher who administers the baseline assessments will be unaware of which treatment group the patient will be assigned. This researcher will be different from the one who will facilitate the rest of study assessments by means of an online procedure. Midwives and obstetricians will be also unaware of the patients’ randomized assigned group for as long as possible. In addition, the statistician who will conduct the primary analysis of the data will be blind to which condition the patient is assigned.

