### Instruments

All participants included in the trial will be assessed at pre-test/baseline, post- intervention, and at three and six months after childbirth (approximately six and 12 months after inclusion). The study instruments that will be used are summarized in Table 1.

**Table 1 Tab1:** Study instruments

Variable	Area	Type	Time	Application
MINI	Psychiatric disorders	Nominal	Baseline	Researcher A (screening)
Sociodemographic	Age, marital status, education, occupation, nulliparity, and previous episodes of depression	Various	Baseline	Researcher A (baseline)
EPDS	Perinatal depression	Treated as interval	Baseline, post-treatment, and 3-month and 6-month follow-up	Researcher A (baseline) Online (follow-ups)
PSS	Perceived stress	Treated as interval	Baseline, post-treatment, and 3-month and 6-month follow-up	Researcher A (baseline) Online (follow-ups)
PANAS	Positive and negative affectivity	Treated as interval	Baseline, post-treatment, and 3-month and 6-month follow-up	Researcher A (baseline) Online (follow-ups)
FFMQ	Facets of mindfulness	Treated as interval	Baseline, post-treatment, and 3-month and 6-month follow-up	Researcher A (baseline) Online (follow-ups)
SCS	Facets of self-compassion	Treated as interval	Baseline, post-treatment, and 3-month and 6-month follow-up	Researcher A (baseline) Online (follow-ups)
EEP	Satisfaction and self-efficacy feelings about motherhood	Treated as interval	3-month and 6-month follow-up	Online (follow-ups)
CSRI	Use of health and social services	Treated as interval	Baseline and 6-month follow-up	Researcher A (baseline) Online (follow-up)

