### Analysis strategy

Results will be reported according to the CONSORT guideline statement [64]. Sociodemographic data at baseline will be presented by means of frequencies (percentages), medians (interquartile range), and means (SD), according to their level of measurement and statistical distribution. Visual inspection on the baseline data will be carried out to check the success of randomization through the two treatment conditions.

The primary efficacy analysis will use an intention-to-treat (ITT) base comparing the main outcome – EPDS – between arms in all the time points as a continuous variable. We will use a repeated measures (RM) design using linear mixed-effects regression models, including participants and the corresponding health center in the random part of the model, by means of the restricted maximum likelihood method (REML). Estimations of slope coefficients (and their 95% confidence intervals [CI]), adjusted for age, nulliparity, previous episodes of depression, and timing of receipt of intervention, will be calculated. To observe the specific trajectories through the study and to evaluate whether possible differences caused by the condition treatment are consistent over time, we will consider the “treatment × time” interaction. In parallel, a per-protocol analysis, with a minimum dose assumed to be ≥ 50% attendance [65], will also be carried out.

If missing data occur in the sample, multiple imputations by using chained equations to replace missing values will be calculated after ensuring data are missing at random (MAR), and as long as there are < 40% missing data in the corresponding variable to ensure validity of imputations [66]. Cohen’s *d* statistic, as an effect size (ES) measure of group differences will be estimated by means of pooled pre-test SDs to weight for the differences in the pre–post means [67]. Values of *d* = 0.20 are regarded as small, 0.50 as medium, and 0.80 large. Secondary analyses will comprise the PSS, PANAS, FFMQ, SCS, and EEP, and will use the same analytical strategy described above.

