Cost-effectiveness and cost-utility procedures of analysis will also be conducted calculating incremental cost-effectiveness (ICER) and incremental cost-utility (ICUR) ratios. The effectiveness of the interventions will be estimated by means of the difference between the EPDS score at baseline and at follow-up; utility will be estimated using quality-adjusted life-year (QALYs) at follow-up. QALYs will be calculated using the area-under-the-curve (AUC). In addition, cost-utility planes will be plotted.

The overall alpha level will be set at 0.05 using two-sided tests and considering Benjamini–Hochberg’s correction for the primary outcome analyses as a way to balance between errors. However, no corrections will be made for secondary outcome analyses.

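### As worded, the cost-effectiveness effect is an EPDS change score with no stated baseline adjustment; unadjusted, this is unbiased but less precise than it need be

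*Protocol article*

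**What the plan says.** The economic paragraph of the Analysis strategy section plans "calculating incremental cost-effectiveness (ICER) and incremental cost-utility (ICUR) ratios". It defines the effect that enters the first of these: "The effectiveness of the interventions will be estimated by means of the difference between the EPDS score at baseline and at follow-up". It does not say how the between-arm increment is computed from that quantity, and it does not mention baseline EPDS as a covariate.

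The primary analysis in the same section is a linear mixed model "comparing the main outcome – EPDS – between arms in all the time points as a continuous variable". Its estimates are "adjusted for age, nulliparity, previous episodes of depression, and timing of receipt of intervention", and on the time course the article says "we will consider the “treatment × time” interaction". Baseline EPDS is not in the covariate list. Cohen's d is also built on pre–post mean differences.

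Under Instruments, participants "will be assessed at pre-test/baseline, post- intervention, and at three and six months after childbirth". Table 1 schedules the service-use inventory (CSRI) at baseline and six months only. Allocation is made "using a simple – not stratified – random number sequence", with 61 women per arm planned.

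**The concern.** Subtracting the baseline score from the follow-up score gives baseline a fixed weight of one. If the two measurements have similar spread and correlate at r below 1, the weight that minimises variance is r, so simple subtraction over-corrects. Here baseline falls in pregnancy and the last assessment about 12 months after inclusion, so a correlation well below 1 is plausible, although the article gives no value.

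The contrast is the denominator of a ratio, where avoidable noise is unwelcome. The Clinical implications section ties wider implementation in Spain to the cost-effectiveness result, so precision has some practical value even though the analysis is secondary.

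**Working it through.** The article states no precision for the ratio and no value of r, so there is no figure of its own to reproduce.

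**Inputs**
- From the article: 61 women per arm; dropout of 15%–20%; planned d = 0.59 (all from Sample size).
- Assumed: r = 0.3, 0.5, 0.7 and 0.8; equal EPDS SD at baseline and follow-up; exactly equal arms.

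**Step 1: standard errors (SD units, n per arm)**
- Unadjusted change contrast: √(2(1 − r) × 2/n)
- Baseline-adjusted contrast: √((1 − r²) × 2/n)
- Ratio of the two: √(2(1 − r)/(1 − r²)) = √(2/(1 + r))

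With 20% dropout, 61 × 0.8 = 48.8, or about 49 completers per arm.

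| r | Change / adjusted, n = 61 | Change / adjusted, n = 49 | SE ratio | Excess SE |
|---|---|---|---|---|
| 0.3 | 0.214 / 0.173 | 0.239 / 0.193 | 1.24 | 24% |
| 0.5 | 0.181 / 0.157 | 0.202 / 0.175 | 1.15 | 15% |
| 0.7 | 0.140 / 0.129 | 0.156 / 0.144 | 1.08 | 8% |
| 0.8 | 0.115 / 0.109 | 0.128 / 0.121 | 1.05 | 5% |

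**Step 2: the same loss seen as sensitivity to chance imbalance**

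The standard error of the baseline mean difference is √(2/61) = 0.18 SD. A gap of that size moves the change contrast, relative to the adjusted one, by (1 − r) × 0.18:
- r = 0.3: 0.13 SD, about 21% of d = 0.59
- r = 0.5: 0.09 SD, about 15%
- r = 0.7: 0.05 SD, about 9%

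This is not a second harm. Since 2(1 − r) = (1 − r²) + (1 − r)², the variance of the change contrast is the adjusted variance plus the variance of this shift. At r = 0.3 and n = 61, 0.173² + 0.127² = 0.046, and √0.046 = 0.214, as in the table.

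**Step 3: does using change as the outcome rule out adjustment?**

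No. If follow-up − baseline = a + τ × arm + β × baseline, then follow-up = a + τ × arm + (β + 1) × baseline. The arm coefficient τ is identical. What matters is whether baseline EPDS is in the regression.

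**Step 4: relation to the primary contrast**

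Six complete datasets were simulated (61 per arm, four visits, SD 4 points, r = 0.3, 0.5 and 0.7). Each was fitted with a mixed model that treats baseline as a response and time as categorical. The six-month treatment × time coefficient equalled the unadjusted change difference to four decimals every time (for example −3.4665 and −3.4665). The baseline-adjusted estimate in that dataset was −3.0735. Across the six datasets the adjusted and change estimates differed by 0.06 to 0.50 points, which divided by the SD of 4 is 0.01 to 0.12 SD.

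**The case against.** The strongest reply is that the article names an outcome quantity, not an estimator. It never says that the contrast is unadjusted, and step 3 shows that a change outcome is compatible with full baseline adjustment. This stands as far as it goes: lack of adjustment is the plain reading of the sentence, not its wording. The gain from adjustment is also a general statistical result, r is unknown, and the penalty shrinks to 5% at r = 0.8. What remains is that the one sentence defining the effect points to simple subtraction, and baseline EPDS is already collected.

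Three stronger readings are tempting, and the document does not support them.

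- **That the economic effect contradicts the trial's own primary estimate.** A reader might infer this because the primary model is covariate-adjusted. But baseline EPDS is not among its listed covariates, its treatment × time contrast is itself a difference in change when time is categorical and data are complete (step 4), and Cohen's d uses pre–post differences as well. The other covariates, missing data or a linear time term could produce some divergence, but that would not come from baseline adjustment.
- **That the plan fails to adjust costs for baseline service use, or to model cost and effect jointly.** The article gives no cost model at all. That is detail a condensed article may leave to the full plan.
- **That unstratified allocation is to blame.** The 0.18 SD figure applies to any equal allocation that does not balance on EPDS, so the randomisation method adds little.

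**Conclusion.** The point holds as a narrow matter of efficiency. If the effect is computed as the sentence reads, the contrast is unbiased under randomisation, but its standard error is about 24%, 15%, 8% and 5% larger than necessary at r = 0.3, 0.5, 0.7 and 0.8. This rests on the assumed r, on equal SDs at the two visits, and on reading the sentence as an unadjusted comparison.

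The effect on the ratio itself cannot be sized, because its uncertainty also depends on costs and the document gives no cost figures. Severity is low: the analysis is secondary, and nothing here affects the validity of the primary result.

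**What to change.** Add one sentence to the economic paragraph: the incremental EPDS effect will be estimated at the six-month visit by regression on arm, with baseline EPDS and the covariates already listed for the primary model. Six months is the natural visit because it is the only follow-up at which the CSRI is collected. Either change or follow-up score may be the outcome, since the estimate is the same.

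The cost is a sentence and a standard model; all variables are already scheduled. There is one small downside. Because the primary model does not list baseline EPDS, the adjusted economic effect may differ somewhat from the primary treatment × time contrast (0.01 to 0.12 SD in the six simulated datasets). Either state how the two relate, or take both from a single baseline-adjusted model.

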## Discussion

MBPs are effective alternative strategies for improving mental and physical health and wellbeing [65], for reducing symptoms of depression [22], for preventing depression relapse [68], and for managing pain and reducing stress [25, 26, 69]. They have also been proposed as potentially beneficial for expectant parents preparing for childbirth for managing pain during pregnancy and labor, reducing the risk of PD, and increasing the availability of parental attention for the infant [70]. With these last aims, several MBPs have specifically been adapted for this population [32–35, 37–39]; some of them have also included compassion techniques [40, 41].

No particular difficulties are expected in relation to recruitment of participants for the present study. However, since recruitment of participants will depend to a large extent on the attitudes of the PC providers who will be recommending the program to their patients, the study will be explained to them in detail before recruitment begins. It is expected that by providing this pre-recruitment information to PC physicians, possible negative attitudes about the study will be minimized.

Other potential difficulties may be that since patient participation in the study will be voluntary, there could be a higher rate of drop-out due to unforeseen life circumstances or conditions arising from the health of the mother or baby. Additionally, the only measures to be used in this study will be self-report questionnaires. Therefore, the data collected will have the limitations of this particular methodology.

### Clinical implications

To the best of our knowledge, this is the first study aiming to implement an adapted MBCP program which specifically adds a compassion component for preventing and treating PD in the Spanish healthcare context. If positive results are achieved, it could have a high impact on this important mental health issue that affects not only women but their partners and their newborn children [4, 5]. Moreover, if this intervention is cost-effective, it could be economically suitable for implementation in PC health centers throughout Spain. Currently, childbirth education classes in Spain are offered by midwives free of charge in all the PC health centers. If midwives were trained to teach this adapted MBCP program, pregnant women, their infants, and their partners might experience important and multiple benefits that come from learning mindfulness and compassion skills and practices for preventing PD.

## Trial status

The protocol version is 3 (25/09/2018). Recruitment began on June 2017 and will finish approximately on June 2019.

## Data Availability

All study information will be confined in secure drawers with limited access. Electronic data files will be password-protected. Participant codes and personal information will be stored in a separate password-protected file. Only the researchers directly involved in the study will have access to the dataset. Paper-based data entry will be double-checked and possible out-of-range values will be revised. The study results will be presented via peer-review publications and congresses. The datasets used and/or analyzed during the current study will be available from the corresponding author on reasonable request.

## Appendix

**Table 2 Tab2:** Elements of the adapted MBCP program

Class	Key concepts	Formal mindfulness practices	Interpersonal mindfulness practices	Formal home practices	Informal home practices
1	Participants learn how present moment awareness during labor and delivery can support the normal physiology of childbirth and may help develop a healthy, compassionate relationship between parent and child and between partners	Raisin meditation Awareness of Breathing meditation	Group sharing about personal and interpersonal changes in pregnancy provides couples the opportunity to normalize the stresses they may be experiencing and start creating a safe and nurturing environment among the participants	15-min Awareness of Breathing practice with audio recordings	Participants are encouraged to bring present moment awareness to routine activities of daily living, such as walking, taking a shower, driving, brushing their teeth, and preparing meals. This practice begins to set the foundation for a more responsive and less reactive parenting
2	Guided reflection about the motivation to participate in the intervention provides expectant parents an opportunity for sharing hopes and fears about pregnancy, childbirth, and parenting The Body Scan is introduced as a tool that helps participants to: • increase body awareness; • learn to be with sensations that are pleasant, unpleasant, and neutral; • experience the impermanence of physical sensations; • notice reactivity regarding thoughts and emotions in relation to physical sensations; • connect with the unborn baby; • begin to develop the skill of uncoupling the sensory component of pain from its emotional and cognitive components	Awareness of Breathing meditation Body Scan Being with Baby practice	Group sharing about guided reflection and group inquiry after Body Scan meditation promotes participant’s feelings of connection and common humanity	Continue Awareness of Breathing 5–10 min every day (with or without audio recordings). 30-min Body Scan with audio recordings	Continue Mindfulness of Routine Activities Practice of Being with Baby throughout the day, using the sensations from the baby’s movements as an opportunity and a reminder to come back to the body and the present moment
3	Participants learn - how fearful anticipations of pain may trigger a cascade of adverse stress reactions that can negatively affect the process of childbirth through the mind–body pathways of the neuroendocrine system - how mindfulness supports the normal physiology of labor with an attitude of acceptance and openness - the difference between primary and secondary suffering and how mindfulness helps participants be with the intense physical sensations of childbirth without adding the secondary suffering of reactivity - that moments *between* contractions can be experienced with equipoise and calm rather than with fear or worry about future pain or negative memories of past pain	Awareness of Breathing Meditation Compassionate Body Scan	Sharing in small groups of three or four about participant’s experiences practicing the Body Scan facilitates participants connecting at deeper levels as a community of practice Large group inquiry to share experiences practicing the Body Scan at home encourages participants to address and normalize common challenges	Continue Awareness of Breathing 5–10 min every day (with or without audio recordings) 30-min Body Scan with audio recordings	Continue Mindfulness of Routine Activities Continue Being with Baby practice Pleasant Events Calendar
4	Mindful Yoga adapted to pregnancy is introduced for the first time Noticing sensations of stretching and contracting and paying attention to the times of ease between poses prepares participants for noticing sensations of contracting and the moments of ease between contractions during childbirth Phrases from Loving-kindness practice during ice pain practice are also introduced. This practice may be especially useful for partners, who can sometimes experience empathic distress and feel helpless to alleviate their pregnant partner’s pain during labor	Sitting Meditation Yoga Practice Pain Practice with ice cubes to induce unpleasant sensations. A variety of mindfulness practices are offered, including - Breath awareness - Focusing attention directly on the unpleasant physical sensations - Moving awareness back and forth between sensations in the hand and the breath - Counting breaths - Turning up the corners of the mouth - Visualizing an image of a baby - Abiding in a safe place - Practicing a Body Scan between “ice sensations.” - Expanding awareness to the body as a whole, noticing where painful sensations are not present and how much of the body is not in pain	Large group inquiry and small group sharing about pleasant events in daily life during the week. Partners are also taught the pain practices in order to let them understand from their own experience how to offer labor support with calm and ease	Continue Awareness of Breathing practice 5–10 min every day Alternate yoga with the Body Scan Participants are encouraged to do at least one sequence of pain practices for 20–30 min, alternating 1-min holding ice using a variety of options with 1.5 min of Awareness of Breathing between the “ice contractions”	Continue Being with Baby practice Continue Mindfulness of Routine Activities, bringing awareness directly to any stress reactions (the contractions of life) experienced during the week Informal Pain Practice: Bring attention to any physical discomforts such as back pain, sciatica, shortness of breath, or heartburn. Practice being with whatever sensations are present, even if they are unpleasant or challenging Unpleasant Events Calendar
5	During the ice practice, both partners receive instruction for using mindful, compassionate touch and also experiment with various postures that might be used during labor, such as child’s pose, side lying, gently rocking side to side or back and forth while standing or sitting These practices may be very beneficial for partners for supporting pregnant women during childbirth contractions	Sitting Meditation, including sound as an object of awareness Mindful Yoga 3 Step Breathing Space Pain Practice 2: Working with partners using compassionate touch	Small and large group inquiry about participants’ experiences with mindfulness and compassion practices and the observations regarding pleasant and unpleasant experiences from the home practice of keeping the pleasant and unpleasant events calendars. Exploration of topics such as reacting or responding, desire and attachment, aversion and resistance and their relationship to secondary suffering in childbirth, parenting, and any experience in life	Continue Awareness of Breathing practice 5–10 min every day Continue to alternate yoga with the Body Scan Participants are encouraged to do at least one sequence of pain practices for 20–30 min, adding compassionate touch practices with their partner, making sure each of them has a turn being touched and touching and discovering what is useful for them	Continue Being with Baby practice. Continue Mindfulness of Routine Activities. Continue informal pain practice when physical discomforts arise in everyday life. Mindful Pooping for both expectant parents. 3 Step Breathing Space several times each day
6	Introduction to vocalizing low-pitched sounds as a way to focus attention and to work with intense body sensations during the ice practice Couples are encouraged to use all the previous practices they have learned in classes 4 and 5 to cope with the intense sensations of “ice contractions”	Sitting Meditation, including thoughts, emotions and choiceless awareness Mindful Yoga 3 Step breathing space Pain Practice 3: Full Immersion in very cold water	Teaching about causes and conditions and using mindful awareness for making wise choices in childbirth such as selection of a care provider and place of delivery Participants learn that the future is unknown, and there is no one “correct way” to give birth and that with continued practice they will have a variety of skills to work with pain and whatever may come during the birth process	Alternate sitting meditation with either the Body Scan or yoga One sequence of pain practices for 20–30 min integrating all the tools learned in classes 4, 5, and 6	Continue Awareness of Breathing practice 5–10 min every day and/or 3 Step Breathing Space Continue Being with Baby practice Continue Mindfulness of Routine Activities, including mindful pooping Continue informal pain practice when physical discomforts arise in daily life
7	Participants learn how mindfulness can help them cope with the biological, emotional, and social needs of a newborn and challenges that may appear during the postpartum period. Fears about the future and how to foster happiness and wellbeing in one’s self and one’s partners are addressed in an interpersonal mindful speaking and listening inquiry. A practice of self-compassion is introduced for the first time here	Sitting meditation Mindful Yoga 3 Step Breathing Space Loving-kindness meditation (including baby, oneself, partner, loved ones, all babies, and parents in the room, a neutral person, a difficult person, and finally all beings everywhere) Walking meditation Mindful speaking and listening inquiry Self-compassion meditation	Large group inquiry exploring participants’ experiences of Loving-kindness and self-compassion practices Interpersonal mindful speaking and listening inquiry between partners. This practice promotes an experience of feeling the authentic presence of the other person, of being seen and heard, as a valuable skill for parenting and partnership	Sitting Meditation with audio recordings. Alternate with either the Body Scan or yoga One sequence of pain practices for 20–30 min, integrating all the tools learned in classes 4, 5, and 6	Continue Awareness of Breathing practice 5–10 min every day. Continue Being with Baby practice. Experiment with adding phrases of Loving-kindness to this practice. Continue Mindfulness of Routine Activities, including mindful pooping. Continue informal pain practice when physical discomforts arise in everyday life Participants are encouraged to begin bringing attention to how they will find support for themselves as a newly birthed family during the early postpartum period 3 Step Breathing Space: several times throughout the day, particularly when feeling stress, as a preparation for postpartum there will probably be less time for formal meditation practice
8	Participants learn how the continued practice of mindfulness and compassion skills during postpartum may - promote resonance, attachment and bonding with the baby; - support the normal physiology of breastfeeding; - help to alleviate the stress of sleep deprivation and meeting the needs of a newborn Symptoms of postpartum blues and depression in both women and men are reviewed, including how to obtain help from a health provider if necessary. Course review and closing ceremony	Sitting Meditation, including thoughts, emotions and choiceless awareness Mindful yoga 3-Step Breathing Space Loving-kindness final meditation	Reflections on what participants have learned throughout the program and final sharing with mindful listening and speaking Participants are encouraged to continue their practice and, if possible, to continue to meet after the formal course ends, forming a community of support for sustaining the practice of living and parenting mindfully	Participants are invited to practice meditation for 30 min each day without the audio recordings in the coming weeks They are also encouraged to continue to incorporate Loving-kindness and self-compassion into their formal practice and daily life	Continue Awareness of Breathing 5–10 min every day Continue Being with Baby practice. Experiment with adding phrases of Loving-kindness to this practice Continue Mindfulness of Routine Activities, including mindful pooping Continue informal pain practice when physical discomforts arise in everyday life Pay attention to bringing mindfulness into communication with others (mindful speech) Continue practicing the 3-Step Breathing Space
9	The class reunion that takes place 3 months after birth is an opportunity for the new parents to reconnect, to meet each other’s babies, and to reflect on what they learned from their birth experience Participants are invited to share how they are applying mindfulness and compassion skills in parenting, how they are growing together as new parents and to express appreciation to and about their partner and themselves Postpartum blues and depression and challenges in breastfeeding are also addressed, including how to seek help from a health provider if necessary	10-min practice of sitting meditation with babies 10-min practice of loving kindness meditation and self-compassion meditation with babies	Large group sharing about how they applied mindfulness and compassion practices to their experiences of birth and how they are using these practices to help them cope with postpartum challenges. Participants are again encouraged to continue to meet to support their ongoing use of mindfulness and compassion practice as a foundation for living and parenting mindfully	3-Step Breathing Space several times a day when possible Self-compassion and loving-kindness practice when possible	Continue informal practice while breastfeeding, taking care of their baby, and doing daily activities Participants are encouraged to do some formal practice or return to formal practice as their babies grow
10	This class takes place as a reunion 6 months after giving birth. Participants share how to apply mindfulness and compassion skills to - the challenges of postpartum and breastfeeding; - going back to work; - finding childcare; - adapting to their new roles, including the changes in their relationship as a couple and with their families of origin	10-min practice of sitting meditation with babies 10-min practice of Loving-kindness meditation and self-compassion meditation with babies	Large group sharing about their experiences of parenting and how they are using mindfulness and compassion practices creatively in this period of their lives	3-Step Breathing Space several times a day when possible Self-compassion and loving-kindness practice when possible	Continue informal practice while breastfeeding, taking care of the baby, at work and doing daily activities Participants are encouraged to do some formal practice or return to formal practice as their babies grow
